The study population is the general community located in 21 CHCs of Pamekasan District. The participating CHCs have already been randomly allocated to either the intervention or control group using a computer-generated sequence by an independent statistician. The intervention group comprises Tlanakan, Bandaran, Pademawu, Sopaah, Galis, Larangan Bedung Kadur, Batumarmar, Teja, and Kowel, and the control group comprises Larangan, Talang, Proppo, Panaguan, Palengaan, Pakong, Waru, Tampojung Pregi, Pasean, Pengantenan, and Bulangan Haji. Allocation concealment was ensured by using sequentially numbered, sealed, opaque envelopes, opened only after enrolment of each cluster. Research assistants will enroll participants through door-to-door recruitment*.* To reduce information contamination, we will ensure geographical separation of intervention and control CHCs where feasible. Pamekasan District, located on Madura Island in East Java Province, covers an area of approximately 792 square kilometers, with a population density of around 850 people per square kilometer. The district is divided into 13 subdistricts, with substantial distances between them; for example, the distance between Batumarmar (a northern subdistrict) and Proppo (a central subdistrict) is approximately 25 kilometers, often requiring over an hour’s travel due to rural road conditions. Given this geographic spread and limited daily intervillage interactions, the risk of information spillover between intervention and control clusters is considered minimal. Baseline and postintervention surveys will be conducted within a short period of a fixed 4-week window across all clusters to minimize variation due to external influences such as health campaigns or seasonal trends. Data collectors will follow the arranged schedule based on the study procedure. For eligibility to participate in the study, participants must be a resident of Pamekasan District, especially in the working area of the 21 CHCs; aged 18-65 years; willing to participate in the study and provide informed consent; and an android or smartphone user. The final criterion might not apply to the control group.

Data regarding the effectiveness of DEDIKASI-app as a strategy to increase awareness and early detection of leprosy and other common skin diseases will be collected using the validated questionnaire that will be developed in phase 2.

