For assessing the effectiveness of DEDIKASI-app as an intervention for enhancing awareness compared to the control group, we will apply an independent sample *t* test if the data exhibit a normal distribution. If the data distribution is not normal, we will use the Mann-Whitney test. All statistical analyses will be performed at a significance level of .05, with a 95% CI (or using the IQR if medians are used).

Missing data will be described and explored. We acknowledge that incomplete case analysis can introduce bias and will consider appropriate imputation techniques during final analysis depending on the extent and pattern of missingness. We will include the outcomes of all participants (intention-to-treat), regardless of the extent the intervention group used DEDIKASI-app.

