### Ethical Considerations

Ethical clearance for the study (all 4 phases) has been sought from the Ethical Review Board of the Faculty of Public Health Universitas Airlangga, Surabaya, with registration number 160/EA/KEPK/2023. The trial in phase 4 has been registered to the INA-CRR, the trial study registry of the Ministry of Health, Republic of Indonesia (INA-O8EX278). Paper-based informed consent will be asked from all participants. Participants will be informed during the consent process whether they will be allocated to the intervention or control group. As such, participants will be aware of whether or not they will be using DEDIKASI-app. This may have influenced their expectations.

All participant data collected via DEDIKASI-app will be stored securely with encryption and password protection. Only authorized HCWs will have access to identifiable information through the HCW interface. Study participants will be informed of data confidentiality, and in case of health concerns, they may be referred to their nearest CHC for follow-up. Research assistants and HCWs involved in the study will receive training on privacy, communication protocols, and referral procedures.

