However, there are several limitations to consider. The first limitation includes potential challenges with digital literacy, limiting generalizability to similar rural populations across Indonesia with large characteristic variation. The study is conducted only in Pamekasan District, Madura Island, East Java, which has specific social and geographical characteristics, potentially limiting the generalizability of the findings. Although this study is limited to community members in Pamekasan District, the design of DEDIKASI-app allows for future use in other settings. The findings will be generalizable to similar rural or underserved populations in Indonesia or other low-resource areas. However, additional evaluation will be needed before applying this intervention in urban or higher-literacy populations or through fully web-based environments. Second, this study may face limitations common to eHealth interventions, including the inability to blind participants, which may introduce expectation bias. This limitation will be mitigated by ensuring anonymity, using validated questionnaires, and cross-referencing with objective measures where possible. Third, while mobile technology enhances accessibility, digital literacy and internet connectivity issues may affect the intervention’s reach and effectiveness. Providing user training sessions and offering alternative offline materials will help ensure broader usability and impact. Additionally, participants’ awareness of being observed or assessed may influence their behavior (the Hawthorne effect) [36]. Lastly, although multiple outcomes will be examined, this pilot study is not powered to control for multiplicity, so findings will be interpreted with caution.

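### Allocation was concealed only up to health-centre entry, so who enrols can depend on arm, and the planned between-arm test states no baseline adjustment

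*Protocol article*

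**What the plan says.** All of this is in the protocol article.

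- **Randomisation (Phase 4).** The unit is the CHC, and allocation is complete: "The participating CHCs have already been randomly allocated to either the intervention or control group using a computer-generated sequence by an independent statistician". The CHCs of each arm are then listed by name.
- **Concealment (Phase 4).** "Allocation concealment was ensured by using sequentially numbered, sealed, opaque envelopes, opened only after enrolment of each cluster".
- **Entry of residents (Phase 4).** "Research assistants will enroll participants through door-to-door recruitment".
- **Eligibility (Phase 4).** Besides residence and age, the criteria include being "willing to participate in the study and provide informed consent; and an android or smartphone user". The next sentence adds: "The final criterion might not apply to the control group".
- **Knowledge of arm (Ethical Considerations).** "Participants will be informed during the consent process whether they will be allocated to the intervention or control group". The same section accepts that this may affect expectations.
- **Between-arm test (Statistical Analysis).** "we will apply an independent sample *t* test if the data exhibit a normal distribution"; otherwise a Mann-Whitney test. No covariate is mentioned, although each respondent has a preintervention interview and a second one about 4 weeks later.
- **Limitations (Strengths and Limitations).** The consequence drawn from open allocation is "including the inability to blind participants, which may introduce expectation bias". The Hawthorne effect is also listed. Recruitment or selection bias is not.

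**The concern.** In a cluster-randomised trial, concealing allocation when clusters enter does not protect the comparison if individuals are recruited later with the arm known. Two steps then lie between randomisation and the analysed sample: who meets the criteria and who agrees. Here both can differ by arm. A resident offered an app may accept for reasons that do not apply to a resident told they are a control. The smartphone rule may admit people to the control group whom the intervention group would exclude.

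Smartphone users may differ from non-users in education, age or prior knowledge, and willing app users may be more ready to learn. Either difference would appear as a between-arm difference in awareness that the app did not cause. A test with no baseline term has nothing to offset it unless change scores are used, and the article does not settle that.

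**Working it through.** No figure in the plan is in dispute here, so the check is mainly of the order of events.

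**1. Sequence.** CHC allocation is described as already done and the arms are named. Recruitment of residents is described in the future tense. Arm is disclosed during consent. So the order is: CHC enters, envelope is opened, resident is approached, arm is disclosed, resident agrees or refuses. Consent would ordinarily come before the first interview, so baseline answers are probably given with the arm known. The article does not state that order outright.

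**2. What the envelopes cover.** They cover the first step only. They cannot hide the arm from a resident who is told it at consent.

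**3. The alternative reading.** Enrolment of a cluster might mean enrolment of all its residents before the envelope is opened. That does not fit allocation already being complete while recruitment lies ahead, nor disclosure of the arm at consent.

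**4. Effect on the comparison.** Suppose the app has no effect. Let *b* be a stable difference in mean awareness between arms caused by recruitment, *m* a difference in gain caused by selection on motivation, *d* a distortion of baseline answers from knowing the arm, and β the within-arm slope of post on pre score. The expected between-arm difference is:

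| Comparison | Expected difference |
|---|---|
| Post-intervention scores, unadjusted | *b* + *m* |
| Change scores | (*b* + *m*) − (*b* + *d*) = *m* − *d* |
| Post scores adjusted for pre score | (*b* + *m*) − β(*b* + *d*) = (1 − β)*b* + *m* − β*d* |

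Change scores cancel *b*. Adjustment reduces *b* when β lies between 0 and 1. Nothing removes *m*.

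**5. Which row applies.** The abstract and the Statistical Analysis section refer to delta change, but the latter does so within the paragraph on phase 3. The paragraph that sets out the between-arm test does not name the score. The first or the second row could apply.

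**6. Illustration, not an estimate.** The document gives no value for *b*, *m* or *d*. Take the first row with *m* = 0, the planning SD of 5 and the expected 600 participants. Assume a 1:1 split and independent observations. Then SE = 5 × √(2/300) = 0.408, and the two-sided 5% test rejects with probability 1 − Φ(1.96 − *b*/SE) + Φ(−1.96 − *b*/SE):

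| Assumed *b* (points) | *b* / SD | Rejection with no true effect |
|---|---|---|
| 0 | 0 | 5% |
| 0.25 | 0.05 | 9% |
| 0.50 | 0.10 | 23% |
| 0.75 | 0.15 | 45% |
| 1.00 | 0.20 | 69% |

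This shows only that an unadjusted comparison of post scores is sensitive to modest imbalance. Clustering by CHC is left out so that the imbalance is seen alone.

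**The case against.** The strongest reply is that the article makes no participant-level claim. The concealment sentence ends with the cluster, and Ethical Considerations says openly that participants know their arm. That stands. A reader might infer that concealment failed or that the statement is false, but the text does not support this. The sentence is true of CHC entry and needs its scope spelled out.

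A reader might also infer that the planned test carries the whole bias. That holds only for post-intervention scores. If change scores are compared, a stable baseline shift drops out.

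Nor does the text show that recruiters chose households differently by arm. The article gives no household-selection procedure for phase 4, and a condensed article may leave that to the full protocol. The documented routes are disclosure at consent and the smartphone criterion.

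Expressing the bias as a share of a detectable difference would be unsound too. The article states no effect size, and one back-calculated from 600 participants would assume individual randomisation, which is not the design.

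Finally, adjustment covariates are often left to an analysis plan. But this article does fix a between-arm test, and that test has no adjustment although a baseline score is collected. The acknowledged biases concern how enrolled people respond. They do not concern who enrols.

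**Conclusion.** The point holds in a limited form. Concealment covered CHC entry only. Residents' entry, and possibly their baseline answers, can depend on allocation through open consent and a criterion that may differ by arm. The article names neither route as a source of selection bias, and its stated between-arm test has no baseline term.

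Neither the direction nor the size of any bias can be derived from the document. It could favour the intervention, through motivated acceptors or smartphone-only entry, or be negligible. The conclusion rests on reading allocation as preceding recruitment, which the text supports, and on consent preceding the baseline interview, which is usual but not stated. It merits correction, mainly because a better analysis is available at almost no cost. It does not show that the trial is biased.

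**What to change.** 1. **Concealment.** State that allocation was concealed at CHC entry only and that participants knew their arm at consent.
2. **Main comparison.** Replace the unadjusted between-arm test with a comparison of post-intervention scores adjusted for the preintervention score, and for demographics where collected. Gender, age, education and occupation are listed for the phase 2 validation study; their collection in phase 4 needs confirming. Fit the model in a form that respects randomisation by CHC. The change-score difference can be shown beside it, since the two respond differently to baseline imbalance.
3. **Sensitivity analysis.** Restrict both arms to smartphone users, if smartphone use was recorded.
4. **Reporting.** Give baseline scores by CHC and arm, with approached, refused and enrolled counts where recorded. State how the smartphone criterion was applied in the control group.
5. **Limitation.** Name arm-dependent recruitment as a bias that adjustment reduces but cannot remove.

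The cost is one clarified sentence, one or more covariates, one restricted analysis, a table and a limitation sentence. Adjustment should also improve precision. Trial data collection had finished at submission, so changing when the arm is disclosed is no longer possible. Because analysis had begun, the report should say whether the adjusted model was fixed before the between-arm results were seen.

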### Statistical Analysis

Results of validity and reliability testing of the community awareness questionnaire developed in phase 2 will be analyzed using both descriptive and analytical statistics. Demographic data will be analyzed descriptively, while the validation and reliability of the questionnaire will be assessed statistically using Pearson correlation and Cronbach α, respectively. Content and face validity will be qualitatively used to avoid question item ambiguity, ensure clarity and relevancy, and ensure that the questions are not judgmental, intrusive, or distressing to target participants [34]. The questionnaire will be administered through an interview setting, with all selected respondents interviewed at 2 points: a preintervention interview and a postintervention interview conducted approximately 4 weeks later (during the intervention study in phase 4).

During the third phase, the questionnaire developed in phase 2 will be used to collect the data on awareness in the general community. All responses to the questions will be given numerical scores based on correct or positive answers. The total score will be calculated, while the mean range will be used to illustrate the distribution and variation of scores. To measure the impact of the intervention, the change in scores (delta change) between preintervention and postintervention assessments will be calculated for each group. The Wilcoxon signed-rank test will be used to compare paired preintervention and postintervention scores within each group. A *P* value of <.01 will be considered statistically significant, indicating improvements in respondents’ knowledge, prevention practices, and health-seeking behavior.

The acceptability test for DEDIKASI-app will be conducted during the third phase, using a survey based on the TAM. A Likert scale will be used as a scoring system. The results from both community members and HCWs will be descriptively analyzed and presented using a frequency table.

Data from the randomized controlled trial in the fourth phase will be analyzed using SPSS version 21 (IBM Corporation). We will conduct a descriptive analysis by calculating the either the mean or median values of the awareness scores and the count of reported common skin disease cases through DEDIKASI-app. The choice between mean or median will depend on the distribution of the scores. We will also use a box plot diagram to visually compare the measurements between the 2 groups.

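### The smartphone-user criterion may be waived in the control arm only, so eligibility can differ by arm after allocation, with a selection bias of unknown size and direction

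*Protocol article*

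**What the plan says.** All of this is in the protocol article.

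- **Eligibility (Phase 4).** After residence and age, the criteria end with "willing to participate in the study and provide informed consent; and an android or smartphone user". The next sentence is "The final criterion might not apply to the control group".
- **Order of events (Phase 4 and Ethical Considerations).** "The participating CHCs have already been randomly allocated to either the intervention or control group", and individuals come afterwards: "Research assistants will enroll participants through door-to-door recruitment". On disclosure: "Participants will be informed during the consent process whether they will be allocated to the intervention or control group".
- **Between-arm analysis (Statistical Analysis).** An independent-samples t test is planned, "test if the data exhibit a normal distribution. If the data distribution is not normal, we will use the Mann-Whitney test". The section also says that outcomes of every participant are analysed under intention to treat, however much the app was used. It states neither a restriction to smartphone users nor an adjustment for smartphone use.
- **Outcome form.** The abstract mentions both total scores and delta change. Statistical Analysis says that "the change in scores (delta change) between preintervention and postintervention assessments will be calculated for each group". Neither place says which of the two enters the between-arm test.
- **Limitations (Strengths and Limitations).** The article notes that "digital literacy and internet connectivity issues may affect the intervention", but this concerns reach and effectiveness. Comparability of the arms is not discussed there.

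**The concern.** Randomising health centres makes the populations behind the two arms comparable in expectation. That protection lasts only if the same people are eligible on both sides. Here an eligibility rule may be applied in one arm and dropped in the other, after allocation. Any resulting difference is systematic, and a larger sample does not shrink it.

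The filter is plausibly related to the outcome, because smartphone users and non-users may differ in age, schooling or prior health knowledge. The article gives no data on this. If they differ in the analysed score, the between-arm difference mixes the effect of the app with the effect of who could be enrolled. Adjusting for smartphone use cannot fully repair this, since the intervention arm contains no non-users by rule.

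**Working it through.** **Inputs from the article (Phase 4, sample size):** two-sided alpha 5%, power 90%, SD 5, 600 participants expected. The two means are not given, so 600 cannot be reproduced as a calculated sample size. It can only be turned into a detectable difference.

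**Assumptions, not in the article:** 300 per arm; individual-level variance only (no clustering); a share *s* of controls who are non-users, 10% to 50% if the waiver was used; a gap *g* in the analysed score (users minus non-users, both without the app) of 1.25 to 2.5 points, that is 0.25 to 0.5 SD, in either direction.

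**Step 1. Detectable difference.**
(1.960 + 1.282) × 5 × √(2/300) = 1.32 points.

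**Step 2. Bias from a control-only waiver.** Intervention participants are all users; controls are a mixture. With no app effect, the expected difference between arms is *s* × *g*.

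| Share *s* | Gap *g* | Bias | Bias / 1.32 | Rejection rate with no app effect |
|---|---|---|---|---|
| 0.10 | 1.25 | 0.125 | 9% | 6% |
| 0.30 | 1.875 (midpoint) | 0.5625 | 43% | 28% |
| 0.30 | 2.5 | 0.75 | 57% | 44% |
| 0.50 | 2.5 | 1.25 | 94% | 85% |

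The rejection rate uses the normal approximation at two-sided 5%. The standard error is √[25/300 + (25 + s(1−s)g²)/300]. For the midpoint row this is √[(25 + 25.74)/300] = 0.411. Then 0.5625/0.411 = 1.37, and the probability of exceeding 1.96 is about 28%.

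If *s* = 0, the bias is 0 and the rate is the nominal 5%.

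**Step 3. Direction.** The sign of the bias is the sign of *g*. With *g* = −2.5 and *s* = 0.30 the bias is −0.75, against the app.

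**Step 4. Which score is compared.** On post-intervention totals, *g* is the level gap between users and non-users. On change scores a stable level gap cancels, and *g* becomes the difference in their four-week change without the app. The article gives no basis for a figure for that.

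**Step 5. Clustering.** With 21 health centres, 600/21 = 28.6 participants each. At an assumed intracluster correlation of 0.01 the design effect is 1 + 27.6 × 0.01 = 1.28, and the detectable difference becomes 1.32 × √1.28 = 1.49. At 0.05 the design effect is 2.38 and the detectable difference is 2.04. The bias in points does not change, but it is a smaller fraction of the detectable difference.

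**Step 6. Restricting to users.** If 30% of 300 controls were non-users, 210 remain: (1.960 + 1.282) × 5 × √(1/300 + 1/210) = 1.46 points. The bias from the waiver is then zero by construction.

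**The case against.** A reader might infer that the arms certainly come from different populations and that the result is biased towards the app. The article supports neither statement.

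- **Whether the waiver was used is unknown.** The wording is tentative, and no share of non-users is reported. Zero is possible.
- **The direction is not established.** Nothing in the article compares awareness in users and non-users. A bias towards the app is likely only if post-intervention totals are compared and users score higher. On change scores it could go either way: faster learning by users would favour the app, while a ceiling among users would work against it.
- **The numbers are illustrative.** The 0.75-point case uses the top of the assumed gap range, so it is not a central value. The 1.32-point yardstick ignores clustering.
- **The criterion is use, not ownership.** Someone using a shared phone may qualify, so figures about ownership would describe another variable.
- **The article is condensed.** Covariate adjustment is commonly left to an analysis plan that is not shown here.

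The first four points stand and limit what can be claimed. The last stands only in part. The arm-specific rule is written in this article, and an analysis plan that restricted the comparison to users would have to depart from the article's commitment to analyse everyone. The tentative wording does not help either, because an optional waiver leaves the control population to field practice.

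**Conclusion.** The point holds in a limited form. The protocol permits eligibility to differ by arm after the health centres were allocated, and its stated comparison does not correct for this. If the waiver was used, the result carries a selection bias of unknown size and direction.

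Under the assumed ranges, the absolute bias runs from 0.13 to 1.25 points, against a detectable 1.32 points (300 per arm, no clustering). These figures show that the bias could matter; they do not estimate it. The matter needs resolving before results are reported, because it bears on the validity of the main comparison.

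**What to change.** 1. **Rule.** Apply the smartphone-user criterion identically in both arms. Because the article reports that data collection has ended, rewriting the sentence changes no enrolment, so the report must also say how controls were actually recruited and whether the waiver was used.
2. **Reporting.** Show smartphone use by arm. If every control was a user, saying so closes the point.
3. **Primary comparison.** Where use was recorded at baseline, compare smartphone users in both arms. State that this defines the eligible population and departs from the article's commitment to include all participants. Name the score compared (post-intervention total or change), since the direction of any bias depends on it.
4. **Sensitivity analysis.** Repeat the comparison with all controls.
5. **If use was not recorded in controls,** state the limitation. A later call-back should not be relied on: it would measure status after enrolment, in one arm only.

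**Cost.** One eligibility sentence, one analysis-set rule and a smaller control group. At 300 versus 210 the detectable difference rises from about 1.32 to about 1.46 points, ignoring clustering. The restriction removes only the bias from the waiver. Any selection from enrolling people after allocation, with the arm disclosed at consent, remains.
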